# Rationale and design of a pragmatic clinical trial to assess the impact of self-monitoring blood pressure at home and self-titration of antihypertensive medication in poorly controlled hypertension: the ADAMPA study protocol

**DOI:** 10.1186/s12875-018-0846-y

**Published:** 2018-09-24

**Keywords:** Self-monitoring, Blood pressure, Hypertension, Self-titration, Primary care, Pragmatic clinical trial

## Abstract

**Background:**

Lack of control of hypertension is one of the most prevalent problems encountered by general practitioners (GPs). Self-measured blood pressure monitoring at home (SMBP) and self-titration of medication could be a good strategy to improve hypertension management, however, evidence is limited and not conclusive. We aimed to assess the effectiveness, in the primary care setting, of an intervention that includes educational components, SMBP and self-titration of antihypertensive medication to decrease systolic blood pressure compared to usual care, in a population with poorly controlled hypertension, during a 12-month period.

**Methods:**

Pragmatic, controlled, randomized, unblinded clinical trial with two parallel groups assigned in a ratio of 1:1 to self-management (which includes educational components, SBMP and self-titration of antihypertensive medication based on a patient’s GP’s pre-established adjustment plan) or to usual care (with educational components too).

**Discussion:**

If the data from this trial show positive results, the study may contribute to a change of strategy in the treatment of hypertension, focusing on the patient as the main actor to achieve blood pressure control. Furthermore, this approach might contribute to the financial sustainability of the National Health Service.

**Trial registration:**

This trial has been registered in the database with reference number EudraCT: 2016-003986-25. Registered 05 May 2017, https://www.clinicaltrialsregister.eu/ctr-search/search?query=2016-003986-25

## Background

The presence of hypertension is one of the most important issues in the global burden of disease [1]. In developed countries, the degree of control of hypertension has increased progressively over the last 15 years and has contributed to a decline in cardiovascular morbidity and mortality [2–8]. However, a recent study carried out in 12 European countries showed that more than 50% of patients treated for hypertension continued to have uncontrolled blood pressure (BP) [9] and that results are far from ideal. As a large part of hypertension management is carried out in primary care (PC) and it is one of the most prevalent problems encountered by General Practitioners (GP), interventions aimed at improving its management should preferably be made in this setting. Recent hypertension clinical guidelines put emphasis on self-measured blood pressure monitoring (SMBP) by patients and on team-based systems to manage the condition [10].

Self-measured blood pressure monitoring at home (SMBP) is practiced extensively nowadays. In the United Kingdom and Canada it is highly recommended by GPs and used by more than 30% of patients [11, 12]. Systematic reviews have shown disparate information regarding the effectiveness of SMBP alone in reducing blood pressure (BP). On the other hand, self-monitoring in conjunction with co-interventions (including systematic medication titration by doctors, pharmacists, or patients; education; or lifestyle counseling) has been shown to lead to clinically significant BP reduction, which persists for at least 12 months. Nevertheless, the effectiveness of SMBP requires additional evaluation given that its definition in those studies is highly heterogeneous (different clinical protocols, different strategies for additional support and management) and given the fact that most studies have short follow-ups (1 year or less) [13, 14].

Regarding home titration of antihypertensive medication, evidence is more limited and shows mixed results. Two clinical essays, the TASMINH2 [15] and the TASMINH-SR [16], both in the United Kingdom and developed in the primary care setting by the same research team, are some of the most recent and interesting clinical trials carried out in this field. In these studies, SMBP together with self-titrate medications (according to a previously agreed plan), combined with telemedicine components, was compared with usual care. In both studies systolic blood pressure (SBP) decreased from baseline to 12 months, with significant differences between the intervention and control group (5.4 and 9.2 mmHg, respectively). Frequency of side effects was similar in both groups [15, 16]. The TASMINH-SR study is of special relevance because it was carried out with high risk patients (with a personal history of stroke, ischemic cardiopathy, diabetes or kidney failure), a population of special interest to achieve BP targets [16]. On the other hand, a clinical trial carried out in the US in a low-income, predominantly minority population, aimed to determine whether health coaching, SMBP and home titration of antihypertensive medications could improve BP control compared with SMBP and health coaching alone. The results showed that both the home-titration arm and the no–home-titration arm had a reduction in SBP, with no significant differences between them from baseline to 6 months [17].

Finally, when interpreting hypertension studies over time, it is important to procede with caution, as the definition of the condition changes almost with every update of guidance. For instance, earlier versions of guidelines such as those of the the Joint National Committee (JNC) and of the European Society of Hypertension (ESH)/European Society of Cardiology (ESC), suggested more restrictive BP control objectives than recent versions (especially in patients over 60 years old, diabetics and patients with renal failure) [18–20]. These objectives may be modified again in the light of the results of recent studies [21–23].

### Study aim

The primary aim of the ADAMPA TRIAL is to assess the effectiveness, in the primary care setting, of an intervention that includes educational components, SMBP and self-titration of antihypertensive medication to decrease SBP compared to usual care, in a population with poorly controlled hypertension, during a 12-month period. In addition, an extension with passive follow-up is planned for 24 months, collecting a reduced set of outcome variables as secondary variables.

### Main research questions

Does a self-management intervention based on SMBP and self-titration medication allow for better control of blood pressure?What is the impact of this intervention on adherence to treatments, lifestyle changes, quality of life, clinical outcomes and use of health services?Is this intervention cost-effective?What are patients’, caregivers’ and health professionals’ views and experiences of SMBP plus self-titration in poorly controlled hypertension?

## Methods

### Study design and setting

The ADAMPA study is a pragmatic, controlled, randomized, unblinded clinical trial with two parallel groups assigned in a ratio of 1:1 to self-management (which includes educational components, SBMP and self-titration of antihypertensive medication based on a patient’s GP’s pre-established adjustment plan) or to usual care (with educational components too).

All participants belong to a Health Area in the Valencia Region (Spain), with a population coverage of 345,500 inhabitants and a geographical area covering the north-east of the city of Valencia and some surrounding towns that are served by sixteen Primary Care Centers (PCC), two Hospitals and a Medical Specialty Centre.

This trial has been registered in the https://eudract.ema.europa.eu/ database with reference number EudraCT: 2016–003986-25.

### Study participants

#### Identification and recruitment

Potential patients eligible to participate in the study will be selected by their General Practitioners (GP) among all patients attending their general practice (case-finding). In their general practice at the PCC, the GPs will inform patients of the study objective and in the case that they meet the inclusion criteria and none of exclusion criteria, GPs will give them the information sheet and informed consent form, responding to all queries and concerns.

#### Eligibility criteria

Eligibility criteria will aim to recruit patients with treated hypertension managed in primary care, who are aged 40 years or older, have a diagnosis of hypertension in their electronic history (coded), have a mean BP reading on the reference arm of SBP > 145 or diastolic blood pressure (DBP) > 90 mmHg on the baseline examination, who voluntarily accept participation in the study and sign the corresponding informed consent. The mean BP will be obtained as follows: In the first visit, BP should be measured on both arms. If there are differences, the reference arm should be that with the highest value of BP. Subsequently, the average BP of at least two measurements, in the sitting position, spaced 1–2 min apart should be calculated. If the first two readings are very different, an additional measurement should be done and the mean BP will be the average of the two readings considered valid [8].

#### Exclusion criteria

Exclusion criteria will include inability to self-manage their BP, including dementia or significant cognitive impairment (at the discretion of the researcher performing the recruitment), a history of orthostatic hypotension (fall> 20 mmHg from SBP after taking the orthostatic position), SBP > 200 or DBP > 100 mmHg in the baseline examination, being prescribed more than 4 antihypertensive drugs, inclusion in another hypertension study or clinical trial, presence of tremor or neurological disease that makes it difficult to perform SMBP, presence of arrhythmia, presence of terminal illness, chronic incapacitation to leave home, an acute cardiovascular event in the last 3 months, hypertension managed directly by other specialist doctors outside the primary care environment, pregnant women or those actively seeking to become pregnant, having a household member already enrolled in the study and non- or temporary residents.

### Randomization

Patients with uncontrolled hypertension will be randomized in a 1:1 ratio to receive either usual care or self-management using a computer randomization system via internet. Minimization will be used [24], taking into account age, gender, SBP > 160 mm HG, diabetes, cardiovascular disease (ischemic heart disease, heart failure, cardiomyopathy and peripheral arterial disease), stroke (chronic stroke) and chronic kidney disease status. Similar approaches have been used in previous clinical trials of self-monitoring in the control of hypertension [15, 16].

### Participant flow through the study

An overview of the schedule of enrolment, interventions, and assessments in the ADAMPA study, according to the SPIRIT guidelines is shown in Fig. 1**.** Each aspect will be described in more detail throughout the present protocol.

**Fig. 1 Fig1:**
[figure not shown]
SPIRIT flow diagram: Schedule of enrolment, interventions, and assessments in the ADAMPA study. *BP* Blood pressure, *SMBP* Self-monitoring blood pressure, *SBP* Systolic Blood Pressure, *DBP* Diastolic Blood Pressure, *PDC* Proportion of Days Covered. * Defined as period of continuous use of the corresponding drug from the beginning of the follow-up until its discontinuation. ** Defined as the number of patients whose pharmacological treatment had not been modified, divided by the number of patients not reaching the target values (SBP and/or DBP measurements taken at 6 and 12 months of follow-up), according to the recommendations of the European Society of Hypertension and European Society of Cardiology

Recruited hypertensive patients who meet the inclusion criteria and none of the exclusion criteria, who have been duly informed (by their GP) of the characteristics of the study, have signed the informed consent and been randomly assigned to the intervention or control group, will proceed as follows:

#### Intervention group

At their practice, the GPs will have established, with each patient in the intervention group, the BP target according to the European Guide for the management of Hypertension 2013 [19] and how to act according to their BP measurements (Fig. 2), including instructions for medication self-adjustment (if necessary). At the same time, the GP will inform them that they will be recalled to make an appointment with a member of the research team, who will provide them with additional information about their self-management of BP and for completing data corresponding to the baseline visit.

**Fig. 2 Fig2:**
[figure not shown]
Instructions to patients: “HOW TO ACT ACCORDING TO YOUR BLOOD PRESSURE MEASUREMENTS” in the ADAMPA study. Adapted and modified from: The Colour Coding Chart. Supplementary webappendix in: McManus RJ, Mant J, Bray EP, et al. Telemonitoring and self-management in the control of hypertension (TASMINH2): a randomised controlledtrial. Lancet 2010; published online July 8. DOI:10.1016/S0140-6736(10)60964-6

Subsequently, patients will be given -and trained in the use of- a validated home blood pressure monitor (Omron M3 model HEM-7131-E), as well as the “Intervention group booklet” containing: the patient’s code, the reference arm on which BP is measured, the BP target, general information and basic recommendations for improving BP control, instructions to manage the home blood pressure monitor, how to act according to their BP (Fig. 2) and the “monthly registration sheets” for a six month period in order to register their blood pressure twice a day, once in the morning and once in the evening (for the first seven days of each month) and to register contacts related to their BP (by phone, regular or urgent consultation at the office or hospital consultation) during that follow-up period.

#### Control group

Patients will be informed by their GP that they will continue their usual care regarding their BP and that they will be recalled to make an appointment with a member of the research team, who will provide them with information and basic recommendations for improvement of BP control and for completing the data corresponding to the baseline visit. Subsequently, members of the research team will deliver the “*Control group booklet”* containing the patient’s code, general information and basic recommendations for improving BP control, as well as the “monthly registration sheets” for a six month period in order to register contacts related to their BP (by phone, regular or urgent consultation at the general practice or hospital consultation) during the follow-up period.

Patients in the control and intervention groups will be informed that the research team will phone them four weeks after the baseline visit to clarify any doubts raised. If necessary, on-site visits will be arranged for further clarification.

Both groups will be contacted by phone at 3 months to clarify any doubts and at 6 months a follow-up visit will be established at the PCC, where the corresponding variables will be collected. The same will be done at 12 months. The follow-up variables will be collected up to a maximum of 6 weeks after the end of the follow-up period. An extension of the study will be performed with passive follow-up at 24 months, collecting a reduced set of outcome variables as secondary variables. Participants’ flow through the trial is outlined in Fig. 3.

**Fig. 3 Fig3:**
[figure not shown]
Participants’ flow through the study. *GP* General Practitioner, *SBP* Systolic Blood Pressure, *DBP* Diastolic Blood Pressure, *BP* Blood Pressure, *SMBP* Self-Management of Blood Pressure

Patients have the right to leave the study at any time. In addition, the researcher may discontinue a patient from the study if deemed necessary for any reason including: non-eligibility (retrospective if not detected at the time of inclusion, or prospective e.g. pregnancy during the follow up), an adverse event or disease progression involving incapacity to comply with trial procedures.

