### Intervention

#### Intervention group

##### Blood pressure self-monitoring

Patients will be trained to perform SMBP by the research team through a validated home blood pressure monitor (Omron model M3 HEM-7131-E). Patients will take their BP in the morning and in the afternoon, every day of the first week of each month. This will be done in the morning, before breakfast and before taking their medication (between 6 am. and 9 am.) and in the evening before dinner and before taking their medication (between 6 pm. and 9 pm.). These measurements will be recorded by the patients for the first seven days of each month on the “monthly registration sheets” located in the “*Intervention group booklet*”. If patients want to monitor their BP during the remaining weeks of the month, it is recommended that they just do so one day a week. Patients are instructed to act according to a table that contains easy-to-follow colour coded action steps. This guideline prompts the patient to contact the GP or visit the health center when BP values are very high or very low. Four or more above target readings in a month will require a change in medication (See Fig. 2).

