### Statistical analysis

Analysis will be on an intention-to-treat basis for complete cases. We will use mixed models (general linear modeling –GLM) to compare SBP at 12 months between the intervention and control groups. This analysis will be presented in both crude and adjusted forms for the different covariates of interest (baseline BP, gender, GP/PCC-random effect, diabetes, etc.). A sensitivity analysis will be performed to examine the potential effect of missing data, which will include substitution by multiple imputation, replacement of data lost by the most recent data or by the mean of the series. Additionally, analyses of the main outcome measure by subgroups of age, gender, comorbidity, level of chronicity, better control at baseline, etc. will be performed.

Differences in secondary outcome measures (DBP, percentage of patients controlled, PDC, persistence and TI) will be analyzed using methods similar to those used for analysis of the main outcome measure.

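### Researchers who know the allocation may take randomised patients out of the study for any reason, and the complete-case analysis then drops them, which threatens the intention-to-treat comparison

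*Protocol article*

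**What the plan says.** All places are in the protocol article.

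- **Discontinuation rule** (Participant flow through the study, text after Fig. 3): "the researcher may discontinue a patient from the study if deemed necessary for any reason including: non-eligibility". Ineligibility may be found at either time: "retrospective if not detected at the time of inclusion, or prospective e.g. pregnancy during the follow up". The other listed ground is "an adverse event or disease progression involving incapacity to comply with trial procedures".
- **Blinding** (Study design and setting): the trial is a "pragmatic, controlled, randomized, unblinded clinical trial with two parallel groups assigned in a ratio of 1:1 to self-management" or usual care.
- **Analysis set** (Statistical analysis): "Analysis will be on an intention-to-treat basis for complete cases". Missing data are addressed in a sensitivity analysis, "which will include substitution by multiple imputation, replacement of data lost by the most recent data or by the mean of the series".
- **Eligibility** (Exclusion criteria): patients unable to self-manage their BP are excluded, at the recruiting researcher's discretion, as are those with "presence of tremor or neurological disease that makes it difficult to perform SMBP".
- **Intervention arm** (Blood pressure self-monitoring): "Patients will be trained to perform SMBP by the research team". This comes after randomisation and applies to this arm only.
- **Control arm** (Participant flow, Control group): a baseline appointment with the research team, a booklet, and monthly sheets for BP-related contacts. Both arms have calls at four weeks and 3 months and visits at 6 and 12 months.

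**The concern.** Intention to treat needs two things: patients are analysed in the arm to which they were randomised, and their outcomes are sought whatever happens to their treatment. The discontinuation rule works against the second. It ends participation in the study, its list of reasons is open, and the person deciding can know the arm. The article does not say that a discontinued patient is still measured at 12 months. If that reading is not taken, the complete-case rule leaves the patient out of the primary analysis.

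The loss need not be balanced. A patient whose tremor or cognition makes home measurement impracticable is more likely to be noticed while being taught to do it, and only one arm is taught. Such a patient can then be declared ineligible in retrospect, while a similar control patient stays in. If those removed would have had higher SBP at 12 months, the patients left in the intervention arm look better than the arm as randomised, and the primary comparison tilts towards self-management. Clinical events could be under-recorded in the same arm if follow-up stops at removal.

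**Working it through.** **Reproducing the plan's own figures.** Inputs from Sample size consideration: difference 5 mmHg, SD 15 mmHg, two-sided alpha 0.05, power 90%, 1:1 allocation.

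- Normal approximation: n per arm = 2 × (1.960 + 1.282)² × 15² / 5² ≈ 189.1, so 190 per arm and 380 in total. The t-based calculation gives 191 per arm, 382 in total, as stated.
- 382 × 1.20 = 458.4, which gives the stated 458.

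The point disputes neither figure. They supply the SD and the arm size used below.

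**How a removed patient leaves the primary analysis.**

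1. The rule permits removal from the study after randomisation, with the allocation known.
2. The article makes no provision for a 12-month reading after removal.
3. The primary analysis is restricted to complete cases.
4. So a patient removed before 12 months and not measured afterwards is not in the primary comparison.

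**Illustration of size.** The article gives no removal rate and no prognosis for removed patients, so these are assumptions: a share p of the intervention arm is removed, their 12-month SBP would have been D mmHg above the mean of the full arm, and no controls are removed.

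- Full-arm mean m = p(m + D) + (1 − p) × (mean of those retained), so the retained mean is m − pD/(1 − p). The bias is pD/(1 − p), in favour of self-management.
- SE = 15 × √(1/191 + 1/[191(1 − p)]).
- Two-sided type I error with no true effect = P(|Z + bias/SE| > 1.96).

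| p | D (mmHg) | Bias (mmHg) | Share of 5 mmHg | SE | Type I error |
|---|---|---|---|---|---|
| 3% | 5 | 0.15 | 3% | 1.547 | 0.051 |
| 5% | 10 | 0.53 | 11% | 1.555 | 0.063 |
| 8% | 15 | 1.30 | 26% | 1.568 | 0.132 |
| 10% | 15 | 1.67 | 33% | 1.577 | 0.185 |

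Worked for the last row: bias = 0.10 × 15 / 0.90 = 1.67; SE = 15 × √(1/191 + 1/171.9) = 1.577; bias/SE = 1.057; type I error ≈ 0.185.

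**Offset by control removals.** If a share q of controls with the same D is also removed, the net bias is pD/(1 − p) − qD/(1 − q). With p = 10%, D = 15 and q = 5%, it is 1.67 − 0.79 = 0.88 mmHg. With q = 10% it is zero.

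**Whether the sensitivity analyses repair it.** Standard multiple imputation assumes data missing at random given what was recorded, and removal related to the unseen outcome violates that. For a patient removed at training, the most recent value can only be the baseline reading. The series mean also stands in for a reading that was never taken. These analyses are useful, but they do not cure outcome-related removal.

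**The case against.** The strongest case on the other side has several parts.

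- **Difficulty with trial procedures is not a free-standing ground.** A reader might infer that patients can be removed simply for failing to keep up with home monitoring. The listed ground ties incapacity to an adverse event or disease progression; only the open phrase about any reason could reach further. This stands.
- **Controls have procedures too.** A reader might infer that trial procedures exist almost only in the intervention arm. Controls have a research-team appointment, sheets, calls and two visits, and an incapacitating illness could stop attendance in either arm. The intervention burden is heavier, but the stronger statement is not supported.
- **Arm dependence is inferred.** GPs check eligibility before randomisation, and controls also meet the research team at baseline, where tremor or cognitive impairment could be seen. This stands as a limit: the asymmetry is plausible, not established.
- **Nothing orders exclusion of existing data.** The article does not say that discontinued or ineligible patients are left out when they have a 12-month reading, or that their events go unrecorded. It is a condensed account, and Figs. 1 and 3 are not visible in the text reviewed. This rules out saying that the comparison is broken.
- **Missing-data analyses are planned.** True, and it bears on severity, though they do not cure the problem.
- **The size is one-sided.** The illustration assumes no control removals. With no true effect, D has to come from prognosis alone, for which the document gives no basis. This stands.

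Leaving the matter to the analysis plan is not an adequate answer. Who stays under follow-up is a conduct rule that this article states, and no analysis plan can recover readings that were not taken.

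**Conclusion.** The concern holds in a limited form. The rule permits removal of randomised patients from the study by people who know the arm, and together with the complete-case analysis it allows exclusion from the primary comparison to depend on arm. It threatens the intention-to-treat comparison. The stronger conclusion, that the comparison is already broken, is not supported: it would require the document to order exclusion of removed patients, or to show that removals will fall in one arm, and it does neither.

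The size cannot be determined from the document. Over 3-10% removal and an excess of 5-15 mmHg, the illustrative bias is about 0.15-1.7 mmHg against a 5 mmHg target, and type I error is about 0.051-0.185 instead of 0.05. At the low end the effect is negligible. Both ranges rest on assumed p and D, SD 15, 191 per arm before removals and no control removals.

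Severity: should-fix. The remedy is cheap, and data not collected cannot be restored later.

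**What to change.** Reword the discontinuation paragraph so that stopping the trial intervention and leaving the study are separate events, without changing when the intervention may be stopped. Then state that:

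1. unless consent is withdrawn or the patient dies, BP at 6 and 12 months and clinical events are sought for every randomised patient, including those discontinued by the researcher;
2. patients found ineligible after randomisation stay in the primary analysis, in their randomised arm;
3. researcher-initiated discontinuations are reported by arm, with reasons.

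The cost is protocol wording and a few further attendances at visits already in the schedule. The effect estimate may be slightly diluted, because patients who stop the intervention or should not have been enrolled remain in the comparison.
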